#### Secondary endpoint analysis

2.10.3

Secondary outcome metrics include the interval between BoNT treatments, improvement rates in motor symptoms (JRS, BSRS, and BFMDRS), quality of life (BSDI, SF-36, and CDQ-24), and subjective efficacy evaluations (PEGR) at different time points. The interval between BoNT-A treatments will be expressed as mean ± SD with differences analyzed using the two-sample t-test if the data follows a normal distribution; otherwise, median and interquartile range will be used, and the Mann–Whitney U-test will be applied. Improvement rates in motor symptoms, quality of life scores, and subjective efficacy evaluations will be expressed as mean ± SD or median and IQR, depending on the normality distribution. Differences between the two groups and their 95% CI will be reported. Outcomes with repeated-measures continuous data will be compared between the groups using repeated-measures ANOVA. Multiple tests will be corrected using Bonferroni correction. All statistical analyses will be performed using SPSS v.25.0 (IBM Corp). *p* < 0.05 will indicate a statistically significant difference.

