### Trial design

2.1

We will conduct a single-centre, open-label, randomised controlled trial. Patients diagnosed with BSP receiving BoNT treatment at our centre will be approached. The protocol follows the Standard Protocol Items: Recommendations for Interventional Trials guidelines (22). Outcomes, including symptom severity, disability, and quality of life, will be evaluated at baseline and at weeks 2, 4, 8, 12, 16, 20, and 24 post intervention. Patients will be asked to complete a self-report questionnaire to document their response to BoNT and the duration of clinical benefits after BoNT treatment. We will recruit only those patients who have received positive benefits from BoNT for less than 12 weeks. We plan to enroll 64 patients and randomly (1:1) assign them to the experimental group (topical FEO combined with BoNT-A injection) or control group [topical coconut oil (CO) combined with BoNT-A injection]. CO will be used as the control because FEO must be diluted 1:1 with CO as the carrier oil (16).

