### Objectives and endpoints

2.3

Primary objectives: The study primarily aims to evaluate the clinical effects of topical FEO combined with BoNT injections in patients with BSP. Specifically, we will compare the topical FEO group with the CO group in terms of the duration of symptom improvement, quality of life, and self-rating of response to efficacy during a 24-week follow-up. Symptom improvement is defined as a decrease of one point or more in the JRS severity in the JRS severity score relative to baseline in patients with BSP (24). We hypothesized that, unlike the placebo group, topical FEO combined with BoNT will significantly prolong the duration of symptom improvement, improve patient rating of quality of life, and self-rating of response to efficacy, with acceptable safety at the 24-week follow-up.

The primary endpoint is the duration of symptom improvement over 24 weeks, as defined above.

The secondary endpoint of the study is the percentage change from baseline to different time points in the physician rating of the BSP. This involves motor symptom severity, measured by the JRS (25), the Blepharospasm Severity Rating Scale (BSRS) (26), and the Burke Fahn Marsden’s Dystonia Rating Scales (BFMDRS) (27), and quality of life, assessed by the Blepharospasm Disability Index (BSDI) (25), the Short Form-36 Health Survey (SF-36) (28), and the Cranio-cervical Dystonia Questionnaire (CDQ-24) (29). In addition, patient subjective ratings via the Patient Evaluation of Global Response (PEGR) and the incidence of adverse events will be included (30).

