### Sample size

2.6

The sample size was calculated using the two-sample t-test method in PASS 15 software (NCSS, LLC, Kaysville, Utah, USA), with a two-sided significance level of 0.05 and a power of 0.8. Based on preliminary clinical observations obtained in our center, topical FEO alone was effective in approximately 50% of patients with BSP. This finding, combined with a conservative estimate of efficacy, prompted a reassessment of the required sample size to ensure adequate statistical power. The revision was implemented after trial initiation but prior to completion of participant recruitment, and constitutes an important protocol modification based on internally generated data. To determine the mean and standard deviation (SD) needed for the sample size calculation, we retrospectively analysed data from 61 patients with BSP at our movement disorders clinic who had received standard BoNT-A treatment and met the study’s inclusion criteria. After receiving their last three consecutive BoNT-A injections, these patients experienced clinical benefits for less than 3 months each time, demonstrating consistently unsatisfactory therapeutic effects. The mean duration of clinical benefits was 73.99 days (SD = 14.28). Given that the control group will receive a placebo, there may have been greater variability in the therapeutic effects due to individual response and disease progression; therefore, we decided to round the mean value to 75 days and the SD to 15 (i.e., 75.0 ± 15.0) to ensure robustness in the calculation. In this study, we hypothesized that combining BoNT-A injection with topical FEO would extend the effective duration of symptom relief by 30 days to 105.0 ± 15.0 days. Given an expected effective rate of only 50%, we estimated the mean duration of benefit in the experimental group as 90.0 ± 18.5 days, reflecting a weighted average between responders and non-responders. The resulting sample size calculation indicated N1 = N2 = 25, meaning that 25 participants are required for each group. Considering the participant loss to follow-up, we determined that each group would recruit 32 participants. A professional statistician verified the sample size calculation method. The amended protocol was reviewed and approved by the Ethics Committee of the First Affiliated Hospital of Sun Yat–sen University.

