### Trial assessment and follow-up

2.9

Full eligibility criteria will be assessed and confirmed before randomization. Further assessments should be conducted at multiple time points. An overview of the data collection process is provided in Table 2. Data will be collected from all participants until they complete the 24-week follow-up period or discontinue the study.

**Table 2 tab2:** Time and events.

Description	Screening	Day 0	2nd week	4th week	8th week	12th week	16th week	20th week	24th week
Consent	**√**								
Neurological exam	**√**								
Medical history	**√**								
Inclusion/exclusion	**√**								
Randomization	**√**								
MRI	**√**								
Baseline assessment	**√**								
Motor symptom assessment	**√**		**√**	**√**	**√**	**√**	**√**	**√**	**√**
Quality-of-life assessment	**√**		**√**	**√**	**√**	**√**	**√**	**√**	**√**
Video recording	**√**		**√**	**√**	**√**	**√**	**√**	**√**	**√**
PEGR			**√**	**√**	**√**	**√**	**√**	**√**	**√**
Non-motor symptom assessment	**√**					**√**			**√**
Blinded rater evaluation	**√**	**√**	**√**	**√**	**√**	**√**	**√**	**√**	**√**
BoNT injection		**√**							
FEO/CO application			**√**	**√**	**√**	**√**	**√**	**√**	**√**
Clinical assessments	**√**	**√**	**√**	**√**	**√**	**√**	**√**	**√**	**√**
Safety assessment	**√**	**√**	**√**	**√**	**√**	**√**	**√**	**√**	**√**

BoNT, botulinum toxin; CO, coconut oil; FEO, frankincense essential oil; MRI, magnetic resonance imaging; PEGR, Patient Evaluation of Global Response.

Patients will be withdrawn for the follow-up during a 24-week observation period if they meet any of the following three conditions: (1) the subject receives a BoNT-A reinjection during the follow-up period, (2) the JRS score returns to the baseline score, or (3) completion of a 24-week follow-up visit.

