### Statistical analysis

2.10

Trial analysis will be performed on an intention-to-treat (ITT) population. No interim analyses will be performed. A full statistical analysis plan will be developed before the final analysis.

Assumptions for parametric tests will be evaluated before analysis. Normality will be assessed using the Shapiro–Wilk test and Q-Q plots, and homogeneity of variances with Levene’s test. If these assumptions are not met, non-parametric alternatives will be used.

Missing data will be handled under the ITT principle, using all available observations without imputation beyond the last completed visit. Mixed-effects models will be used for repeated-measures secondary outcomes under the missing-at-random assumption. A per-protocol sensitivity analysis will also be conducted.

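### Repeated secondary outcomes are assigned both mixed-effects models and repeated-measures ANOVA; a listwise ANOVA over all seven visits would have almost no complete cases

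*Protocol article*

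**What the plan says.** Section 2.10 (Statistical analysis) sets the missing-data rule as "using all available observations without imputation beyond the last completed visit" and then names a method: "Mixed-effects models will be used for repeated-measures secondary outcomes under the missing-at-random assumption".

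Section 2.10.3 (Secondary endpoint analysis) names another: "Outcomes with repeated-measures continuous data will be compared between the groups using repeated-measures ANOVA". It also promises between-group differences with 95% confidence intervals for improvement rates at different time points.

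The outcome scale is set in section 2.3: "The secondary endpoint of the study is the percentage change from baseline to different time points in the physician rating of the BSP". Section 2.1 gives the schedule; symptom severity, disability and quality of life "will be evaluated at baseline and at weeks 2, 4, 8, 12, 16, 20, and 24 post intervention".

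Section 2.9 ends a patient's follow-up before week 24 if "the subject receives a BoNT-A reinjection during the follow-up period" or if "the JRS score returns to the baseline score".

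**The concern.** The two method statements cover the same outcomes, and nothing makes one primary and the other a sensitivity analysis. This is not detail left to the promised analysis plan, because the article fixes both methods and they disagree. If the conflict stays, the choice between them could be made after the results of each are known.

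The methods also treat incomplete follow-up in opposite ways. A likelihood-based mixed model uses every visit a patient attended. Repeated-measures ANOVA in its standard form uses only patients with every included visit, which conflicts with the available-observations rule in section 2.10. Incomplete follow-up is built into this trial: patients leave when their JRS score returns to baseline, and the expected duration of benefit is well short of the last visit.

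**Working it through.** **Inputs**

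- Duration of benefit (section 2.6): control 75 ± 15 days; FEO arm 90 ± 18.5 days, described as a weighted average of non-responders and responders (105 ± 15 days) at a 50% effective rate.
- 32 patients per arm (section 2.6).
- Post-baseline visits at days 14, 28, 56, 84, 112, 140 and 168 (section 2.1, weeks × 7).
- Assumptions: durations are normal; benefit ends at about the time JRS returns to baseline and so triggers exit.

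**The plan's own figure.** A two-sample t-test with difference 90 − 75 = 15 days, SD 18.5 in both arms and two-sided alpha 0.05 has power 0.802 at 25 per group, so the stated 25 reproduces. The 32 recruited fits 20% loss: 25/0.80 = 31.25, rounded up to 32. The duration inputs are therefore taken as the plan's own. The protocol gives no figure for the repeated-measures analysis.

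**Patients still in benefit at each visit** = 32 × P(Z > (day − mean)/SD):

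| Visit | Day | Control | FEO (90 ± 18.5) | Total of 64 |
|---|---|---|---|---|
| Week 8 | 56 | 28.7 | 30.9 | 59.7 |
| Week 12 | 84 | 8.8 | 20.1 | 28.8 |
| Week 16 | 112 | 0.2 | 3.8 | 4.0 |
| Week 20 | 140 | 0.0002 | 0.11 | 0.1 |
| Week 24 | 168 | below 0.001 | below 0.001 | below 0.001 |

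**Complete cases.** The generous reading is that the visit which detects the return to baseline is itself recorded. Week-24 data then require benefit beyond day 140:

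- Control: (140 − 75)/15 = 4.33; 32 × 0.000007 = 0.0002.
- FEO, single normal: (140 − 90)/18.5 = 2.70; 32 × 0.0034 = 0.11.
- FEO, 50:50 mixture of 75 ± 15 and 105 ± 15: the responder half has (140 − 105)/15 = 2.33, tail 0.0098; the mixture tail is 0.0049; 32 × 0.0049 = 0.16.

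The total is about 0.1 to 0.2 patients with all seven visits, nearly all of it from the FEO arm.

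**Sensitivity (assumed values)**

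- FEO 90 ± 30: (140 − 90)/30 = 1.67, tail 0.048; 32 × 0.048 = 1.5 patients past day 140.
- FEO 105 ± 30: (140 − 105)/30 = 1.17, tail 0.122; 32 × 0.122 = 3.9 patients past day 140.
- Control with its SD doubled to 30: (140 − 75)/30 = 2.17, tail 0.015; 32 × 0.015 = 0.5 patient.

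None of these gives a usable between-arm comparison on complete cases.

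**What the mixed model keeps.** On available data it uses essentially all 64 patients, about 60 of them still in benefit at week 8. It does not restore the late visits. Even on the generous reading, the control arm expects 8.8 patients with week-16 data (benefit beyond day 84), 0.2 with week-20 data and 0.0002 with week-24 data. On the same reading week 12 has 28.7 + 30.9; if only patients still in benefit are counted, it has 8.8 + 20.1.

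**The case against.** The strongest reply is that section 2.10 already commits the trial to available data and mixed models, so the plan read as a whole does not rest on complete cases. The group differences at separate time points can also use whoever attends. Listwise deletion belongs to the usual ANOVA procedure, and the article names neither that procedure nor an analysis over all seven visits; an ANOVA limited to early visits would keep most patients. This stands to the extent that the near-zero count is conditional. A reader might infer that the secondary analyses as a whole rest on almost nobody; the documents do not support that. They do leave the ANOVA sentence in force, with no restriction of visits.

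The attendance figures equate the clinical benefit of section 2.6 with the JRS exit trigger. Section 2.9 does not say whether that trigger is the severity subscale or a total score. If it is a total, patients could stay in follow-up longer. That is fair, and is why a range is shown.

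The late-visit loss comes from the exit rule, not from the ANOVA. This also stands: a seven-visit model with unstructured covariance would not be estimable at weeks 20 and 24 on these numbers, so changing the method alone is not enough.

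Other stronger readings fail:

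- A reader might say that the baselines are ignored. They are not, because percentage change divides by baseline. Only a baseline covariate is unstated, which an article may leave to the analysis plan. Table 2 schedules no baseline PEGR, so the point could not apply there.
- Percentage change and Bonferroni correction are legitimate choices; preferring other methods is not a defect in the plan.
- A 22% loss allowance might be inferred from 7/32, but the protocol states no rate, and 20% also gives 32.

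**Conclusion.** The conflict between sections 2.10 and 2.10.3 is real and does not depend on any calculation. Only the mixed model agrees with the available-observations, missing-at-random rule.

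The size is conditional. With a listwise ANOVA over all seven post-baseline visits, and with exit at about the end of benefit, the protocol's durations leave about 0.1 to 0.2 complete cases of 64. A longer assumed FEO duration (105 ± 30 days) leaves about 4 FEO patients past day 140 and still almost no controls.

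One caution applies to the method that survives. Because JRS triggers exit, missing at random is plausible for JRS itself but less secure for the other scales, unless their models use the JRS information.

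The point concerns secondary outcomes only; the primary test in section 2.10.2 is unaffected. It should be corrected before the analysis plan is finalised.

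**What to change.** 1. Delete the repeated-measures ANOVA sentence from section 2.10.3, leaving the mixed model of section 2.10 as the single method.
2. Fit it to the scores, with arm, visit, arm-by-visit and, where one is collected (not for PEGR), the baseline score as covariate. Percentage change can remain as a descriptive summary.
3. Restrict the between-arm contrasts to visits that both arms are expected to reach in adequate numbers, for example through week 12, and name those visits in advance.
4. For the non-JRS scales, state how the JRS course enters the model, for example by modelling JRS jointly as a second response. Entering post-randomisation JRS as an ordinary covariate would adjust away part of the treatment effect.

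The cost is protocol and analysis-plan wording plus some programming for item 4; no new data are needed, and SPSS v.25, the stated software, fits mixed models. The small downside is that no modelled contrast is made at the late visits, where almost no control patients are expected.

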**Methods and analysis:**

This protocol describes an open-label, randomized controlled trial to be undertaken to evaluate daily topical application of FEO and coconut oil (CO) in patients with BSP. The goal is to enroll 32 patients with BSP who have received immediate BoNT injection in each treatment arm. Only patients who have previously received less than 12 weeks of positive benefits from BoNT therapy will be enrolled. The primary outcome will be the duration of symptom improvement after the intervention with BoNT combined with FEO or CO within the 24-week follow-up period. Symptom improvement is defined as a decrease of one point or more in the Jankovic Rating Scale severity score compared to baseline in patients with BSP. Secondary outcomes will consist of changes in BSP symptom severity, disability, and quality of life from baseline to each time point after the intervention. Safety analysis will be based on the presence of localized skin allergic reactions and adverse events. Outcomes will be assessed at baseline and at weeks 2, 4, 8, 12, 16, 20, and 24 after the therapy begins.

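### Plain Bonferroni is named for the secondary outcomes; Holm keeps the same family-wise error on any family, never rejects less, and costs almost nothing

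*Protocol article*

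**What the plan says.** Section 2.10.3 of the protocol article opens "Secondary outcome metrics include the interval between BoNT treatments" and continues with "improvement rates in motor symptoms (JRS, BSRS, and BFMDRS), quality of life (BSDI, SF-36, and CDQ-24), and subjective efficacy evaluations (PEGR) at different time points". That makes eight efficacy outcomes: one interval and seven scales. For the scales, "Outcomes with repeated-measures continuous data will be compared between the groups using repeated-measures ANOVA". The correction is then given in one sentence: "Multiple tests will be corrected using Bonferroni correction". A p-value below 0.05 "will indicate a statistically significant difference".

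The section does not say whether the corrected tests are the outcomes, the visits within a scale, or every scale at every visit. Section 2.3 describes the secondary endpoint as "percentage change from baseline to different time points in the physician rating of the BSP" and singles out no visit. Section 2.10 says that a full statistical analysis plan will follow before the final analysis.

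**The concern.** The definition of the family can properly wait for the statistical analysis plan. The correction method has not been left to it: the article names Bonferroni. For hypothesis tests on a fixed family, Bonferroni is never better than Holm and can be worse, so the stated choice may give up power for nothing.

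This matters more than usual because section 2.3 places quality of life and self-rated response in the trial's hypothesis, beside the duration of benefit. The protocol lists both among the secondary outcomes, so the correction applies to them. The sample size in section 2.6 was set for the primary endpoint alone, so there is little power to spare.

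**Working it through.** **1. The design figure.** Section 2.6 gives means of 75 and 90 days, an SD of 18.5 in the experimental arm, two-sided alpha of 0.05 and power of 0.8. With a common SD of 18.5, the standardised difference is 15/18.5 = 0.81. A two-sample t-test with 25 per arm then has power 80.2%, so the stated 25 per arm reproduces. The calculations below use 0.8 SD for the secondary outcomes. That is an assumption borrowed from the primary endpoint.

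**2. Why Holm cannot do worse.** Order the *m* p-values. Holm compares the *j*-th smallest with 0.05/(*m* − *j* + 1) and stops at the first failure. Every threshold is at least 0.05/*m*, so any p-value that passes Bonferroni also passes Holm. For the error rate, let *m*₀ hypotheses be truly null. The first true null to be rejected must have a p-value of at most 0.05/*m*₀. By the union bound, the chance of this is at most *m*₀ × 0.05/*m*₀ = 0.05, whatever the dependence.

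**3. Power per test under Bonferroni.** Noncentral t with df = 2*n* − 2, noncentrality *d*√(*n*/2), *d* = 0.8. At *n* = 25 the noncentrality is 0.8 × √12.5 = 2.83. At *n* = 32 it is 0.8 × 4 = 3.20.

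| Tests in family | Alpha per test | Power, n = 25 | Power, n = 32 |
|---|---|---|---|
| 1 | 0.05 | 0.79 | 0.88 |
| 8 (one per outcome) | 0.00625 | 0.49 | 0.64 |
| 49 (7 scales × 7 visits) | 0.00102 | 0.27 | 0.41 |

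The visit count comes from the abstract: "Outcomes will be assessed at baseline and at weeks 2, 4, 8, 12, 16, 20, and 24 after the therapy begins". This table shows the effect of family size only. It says nothing about Holm.

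**4. Bonferroni against Holm on the same eight tests.** Simulated normal test statistics, *n* = 25, effect 0.8 SD, correlation 0.5 between all pairs (assumed). Average power over the real effects:

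| Real effects | Bonferroni | Holm |
|---|---|---|
| 1 of 8 | 0.54 | 0.54 |
| 4 of 8 | 0.54 | 0.57 |
| 8 of 8 | 0.54 | 0.65 |

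The Bonferroni figure is 0.54 here and 0.49 in step 3 because the simulation uses the normal rather than the t distribution: the chance of exceeding 2.73 when the mean is 2.83 is 0.54. With all eight effects real, the chance of showing all eight rises from 0.13 to 0.39. Over correlations of 0.3 to 0.7, Holm's average power in that case stays at 0.64 to 0.65.

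**The case against.** Bonferroni is simple, valid and conservative, and choosing it for secondary outcomes is defensible. That stands: nothing here is an error, and the primary analysis is untouched.

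Bonferroni also converts directly into simultaneous confidence intervals, and Holm does not. That stands as a drawback, but a light one. Section 2.10.3 promises 95% intervals without saying that they are adjusted, so they can be reported unadjusted alongside Holm.

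The gain depends on how many effects are real and on a borrowed effect size. That also stands. With few real effects the gain is between nothing and about three points.

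The statistical analysis plan is still to come. That excuses the undefined family, but it does not make the named method the better one.

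A reader might go further and infer that the plan commits to 49 tests, each at about 0.001, so that Holm would bring a very large gain in power. The document does not support this. The number 49 does not appear in it. A repeated-measures ANOVA can give one group test per scale, and the correction could equally apply to visits within a scale. Even on the 49-test reading, most of the recovered power would come from having fewer tests, which Bonferroni could do as well. Taking the other visits out of the controlled family also narrows what the 5% guarantee covers. It is a trade-off and not a free gain.

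**Conclusion.** The point holds as a free improvement. On any family, Holm gives the same family-wise control at 0.05 and never fewer rejections. For eight outcome-level tests the gain in average power runs from nothing (one real effect) through about 3 points (four real) to about 11 points (all eight real). These sizes assume 25 evaluable per arm, an effect of 0.8 SD on each affected outcome and a correlation of 0.5. The superiority of Holm needs none of those assumptions.

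The 49-test case is only one possible reading. If it were intended, power per test under Bonferroni would be about 0.27 at 25 per arm and 0.41 at 32. That would be a reason to think about the size of the family, which is a separate decision from the choice between Bonferroni and Holm.

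**What to change.** Replace the Bonferroni sentence in section 2.10.3 with: *Multiple secondary tests will be corrected with the Holm step-down procedure at family-wise 0.05.* Keep the 95% confidence intervals and label them as unadjusted.

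The statistical analysis plan can then state the family. The natural one is a single between-group test per outcome, eight in all. Stating it is also the occasion to settle which model supplies the test for each scale, since section 2.10 says "Mixed-effects models will be used for repeated-measures secondary outcomes under the missing-at-random assumption" while section 2.10.3 names repeated-measures ANOVA. If the family is limited to one contrast per outcome, the other visits become descriptive. The plan should say so and name the contrasts before data are seen.

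Cost: one sentence, with no new patients, visits or data. Holm needs only the ordered p-values. What is given up is a simple route to simultaneous intervals, which the plan does not promise.
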